# POWIFF- Prospective study of wrist internal fixation of fracture: A protocol for a single centre, superiority, randomised controlled trial to study the efficacy of the VRP (2.0) distal radius plate (Austofix) versus the VA-LCP (Depuy-Synthes) for distal radius fractures

**DOI:** 10.1186/s12891-018-2052-4

**Published:** 2018-04-30

**Keywords:** Distal radius fracture, Volar plating, Functional outcome

## Abstract

**Background:**

Distal radial fractures are one of the most common orthopaedic cases that present to the A&E department. Surgical intervention is warranted in displaced intraarticular fractures and fractures with more than the recommended angulation or shortening, and is most commonly treated with volarly placed fixed angle locking plates. The aim of this study is to determine and compare the efficacy of two different plates for surgical treatment of distal radius fractures. The VRP 2.0 is a new plate produced by the Austofix company and this system will be compared against the VA-LP (Variable angle-locking plate) produced by Depuy-Synthes which has been used as the standard treatment device.

**Methods and Design:**

Patients between the ages of 18 and 80 presenting to the Royal Adelaide Hospital with isolated closed distal radial fractures will be invited to participate in this study. A total of 200 patients are required to provide 90% statistical power at a 5% alpha level to detect a difference of 11.5 points on the PRWE (Patient rated Wrist evaluation) score. The primary outcome measure will be the PRWE score while the secondary outcome measures will include the DASH score, EQ5D score, clinical range of movements, grip strength as well as patient perceived return of function at the wrist and time to resumption to work. These will be measured at 6 weeks, 3 months and 12 months. Radiographic indices including the radial tilt, length, volar inclination and plate prominence will also be measured. Complications will be recorded up to 12 months. Post hoc comparisons will be done using paired t tests. An intention to treat and a per protocol analysis will be done to compare the 2 groups.

**Discussion:**

Distal radial fractures are increasingly being treated by internal fixation using volar locking plates. However, there is no prospective study to date comparing one plate against another in terms of outcome and complications. This study could provide more information about the best way to treat these injuries surgically.

**Trial registration:**

The trial is registered with the Australia New Zealand Clinical Trials Registry (ANZCTR). Trial registration date-17/11/2016. Trial registration number-ACTRN12616001590459.

**Electronic supplementary material:**

The online version of this article (10.1186/s12891-018-2052-4) contains supplementary material, which is available to authorized users.

## Background

Distal radial fractures account for 18% of the cases that present to A&E and are more common in women above the age of 60 [1]. However, there is no consensus within the literature on their management [2]. This is at least in part due to the number of factors which have to be considered when managing these injuries, including age of the patient [3], functional requirements and velocity of the injury. Surgeon [4] and fracture configuration related factors [5] further complicate the treatment algorithm. Operative and nonoperative methods of treatment have been shown to have good results [6].

Surgical management is usually opted for if there is shortening of the radius after closed reduction and splinting of more than 3 mm, dorsal radial tilt of more than 10 degrees and an intra articular step of more than 2 mm [7]. Surgical modalities include, percutaneous K wire fixation, external fixation and, open reduction and internal fixation(ORIF) with an increasing trend recently for surgical management by ORIF using volar fixed angle plates [8, 9]. The advantages of volar fixed angle plates include anatomic fixation, early mobilisation and improved grip strength. The argument for ORIF in the elderly group is that it helps them to keep their level of independence [10] and in the younger patients it allows earlier return to activities [11, 12]. While there are no clinical trials comparing different volar fixed angle devices, there are several biomechanical studies comparing screws versus pegs in fixed angle locking plates [13, 14] as well as various volar fixed angled plates [15]. There are also retrospective follow up studies suggesting that if plates with a lower profile design are used [16] and placed proximal to the watershed line [17], this may result in fewer complications due to tendon synovitis and rupture. Dorsal tendon rupture, after ORIF has also been recognised to be due to improper surgical technique which can be avoided [18]. However, there are no previous studies or randomised clinical trials comparing one plate against another in terms of outcome and complications.

A variety of outcome measures have been described in previous studies following distal radius fractures and include patient related outcome scores, wrist range of movements, grip strength and radiographic parameters. Using multiple outcome measures gives a composite idea of outcome as recent studies have shown that radiological parameters do not always correlate with functional outcome [19]. The Patient Reported Wrist Evaluation (PRWE) score and Disability Arm Shoulder Hand (DASH) score are commonly used to report outcomes in wrist injuries [19, 20]. However, PRWE score has been recognised as the best score for specifically measuring pain resolution and functional recovery in the injured wrist, whereas the Disability Arm Shoulder Hand (DASH) score measures the total upper limb extremity function [21, 22]. Multiple studies investigating distal radial fractures have used the PRWE as its primary outcome score [23–25]. European Quality of Life 5 Dimension (EQ5D) score is a generic health status measurement that is used as a secondary outcome measure in many orthopaedic conditions [26]. The Austofix Company (Australia) have designed a new plate, the “VRP 2.0”, with the purported advantages of having a lower profile and better fragment specific fixation. It allows a variable fixation angle of 40 degrees (compared to 30 degrees for other systems) which in theory allows more fragment specific fixation, and therefore a more flexible and proximal plate positioning. This in turn may help to reduce soft tissue irritation and possible flexor tendon issues. The Austofix plating system has a universal plate which can be used for both the left and right side which helps to reduce the inventory and it’s also less expensive than the comparative plate. The Synthes (West Chester, Pennsylvania) VA-LCP 2.4 distal radius system has been used extensively for distal radius fractures with good results [27] and has been used at the Royal Adelaide Hospital for the last 5 years. There are no studies comparing these 2 systems prior to this and we plan to compare these plates using the PRWE score as a primary outcome measure and the EQ5D, DASH scores as well as other objective radiological and clinical parameters.

### Aims

This study aims to provide high quality evidence for the safety and effectiveness of surgical treatment of distal radius fractures by comparing 2 different plating systems. The primary outcome measure will be the PRWE (Patient rated Wrist evaluation) score between the two plates with the assumption being that the Austofix plate will have a superior outcome with a minimum difference in the PRWE of 11.5 points. The study will also correlate the final PRWE and DASH scores with each other, document the radiographic scores in terms of restoration of radial tilt, height and inclination, correlate the radiographic and clinical scores and document all complications, both major and minor in both groups.

### Objectives

This study is a two armed randomised controlled trial with a parallel observational study. The objectives of this study are to assess the comparative performance of the two plates in terms of outcome scores specific for the upper limb and general health scores, as well as radiographic indices regarding restoration of normal wrist anatomy, plate prominence as well as complications. Secondary outcome measures include the DASH (Disability of Arm, Shoulder & Hand) score and the EQ5D (EuroQol Five –Dimension) score.

### Null hypothesis

The null hypothesis is that there is no difference in the PRWE scores between the two plates being used for wrist fixation in this trial, at the end of 1 year post fixation.

## Methods

The protocol (V 1.2, dated october16, 2016) was prepared in accordance with the Standard Protocol Items; Recommendations for Interventional Trials (SPIRIT) guidelines. This study is funded by the Department of Orthopaedics & Trauma, Royal Adelaide Hospital. The trial will be conducted in accordance with the regulations of International conference on Harmonisation Good Clinical practice (ICH-GCP); all collaborators will be trained in GCP and the trial will be reported in line with the Consolidated Standards of reporting Trials (CONSORT) statement.

### Setting

The Royal Adelaide Hospital(RAH) is one of two level 1 tertiary centres in South Australia and serves a population of approximately 1.7 million. The orthopaedic department manages approximately 200 cases of distal radius fractures with surgery annually.

### Study design

A single centre two-arm randomised controlled trial with a parallel observational study trial design will be completed at the RAH. The study population will be of adults aged between 18 and 80 presenting to the RAH with a closed distal radius fracture and who are considered for surgical treatment using volar plating. Associated ulna fractures will be noted and managed according to the operating surgeon’s preferences, and similarly the distal radioulnar joint.

### Ethical considerations

Ethical approval has been obtained from the Royal Adelaide Hospital Human Research Ethics Committee, Central Adelaide Health Network (CALHN). Adverse effects if any will be documented and notified to the research ethics committee. All participants with complications will be managed as per in-house management protocols. Participants will be covered by the standard South Australian health indemnity arrangements.

HREC reference number: HREC/16/RAH/373.

CALHN Reference number: R20160909, prior to the commencement of this trial.

### Consent procedures

Recruitment and consenting will be done by a trained research associate who will present the trial and interventions in a consistent and unbiased manner. Eligible patients will be provided with an information sheet and will have time to discuss their concerns prior to enrolment. (Patient Booklet and participation form-Additional file 1).

Inclusion Criterion and exclusion criterion are as shown in Table 1. Patients with isolated injuries in the upper limb were chosen so as to avoid the effect other injuries in the same limb could have and therefore bias the outcome. As most of the questionnaires are self-explanatory and to be filled in by patients themselves, reasonable proficiency in English is a pre-requisite.

**Table 1 Tab1:** POWIFF trial - Inclusion and exclusion criterion

Inclusion Criterion	Exclusion criterion
1. Age-18-80	1. Patients with concomitant injuries affecting treatment and rehabilitation of the affected arm
2. Pre-operative DASH score of 30 or less	2. Patients with associated neurovascular injuries requiring immediate surgery
3. Isolated closed distal radius fracture with shortening of radius of more than 3 mm, dorsal radial tilt of more than 10 degrees and an intra articular step of more than 2 mm.	3. Patients with associated significant carpal injuries, including scaphoid fractures
	4. Patient unlikely or unhappy to attend for follow up
	5. Patient with limited English proficiency
	6. Patient without cognitive capacity to consent and participate
	7. Patients with impaired upper limb function prior to injury enough to have a DASH score of more than 30 points

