### Recruitment

All patients eligible for the study, and for whom a decision to undergo surgical treatment by volar plating has been made will be invited to participate. Following patient recruitment to the trial, patients will be randomised to receive one or other of the plates. Patients declining randomisation will be managed using the routine plating option, but will still be monitored longitudinally in the standard fashion, forming an observational arm of the study. Inclusion of the patient in the trial will be flagged on their clinical notes by means of a trial sticker. (See Fig. 1). Documentation of complications such as implant failure, revision to another plate system and cross over will be done.

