#### Secondary outcomes

The DASH score is to be collected as a secondary outcome, in order to assess function of the whole upper limb, at 6 weeks, 3 months and one year [32]. The DASH score has a range from 0 to 100 with higher scores representing greater disability. Subjects rate task difficulty regardless of hand dominance or affected side, thus reflecting their total upper-extremity disability. Both the DASH and PRWE scores have been shown to be ideal and specific as a research tool for the upper limb [30]. The final DASH score at the end of 1 year will be used for definitive comparison between the 2 groups.The EQ5D (EuroQol) score will also be collected as a secondary outcome measure, at 3 months and one year. This score is a validated measure of health related quality of life, consisting of a 5 health domains as well as a separate VAS (Visual analogue) score. The five domains included in the EQ-5D are: mobility; self-care; usual activities; pain/discomfort and anxiety/depression. The EQ5D is the measure that tends to be most utilised in cost utility analysis [33] . The final EQ5D at the end of 1 year will be used for definitive analysis.Complications (including surgical site infection, unplanned surgery, implant failure, loss of reduction/screw breakout or implant fracture and post-operative nerve palsy up to one year) in both groups will also be documented and compared.Surgical data including operation time and screw numbersRadiographic indices including radial height, tilt and inclination and rates of non-union / delayed union and the Soong score will be analysed and compared in both groups.Soong score will be used to assess prominence and profile of the plate [17].The active range of motion (ROM)at the wrist and grip strength at 3 months and one year will be measured.Time to resumption of work and patient perceived percentage return of global function at 6 weeks, 3 months and 1 year.

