### Trial organisation, regulation and oversight

All the cases will be individually reviewed as part of the daily trauma meeting held in the department. All issues pertaining to the management of the trial will be coordinated by the trial management group which will consist of the chief investigator, coinvestigators, trial manger, statistician and the department head. The data management committee will review the trial progress, interim data and safety aspects of the study at 6 months and at completion. The allocated recruitment period for the trial is 24 months. Recruitment will begin in March 2017 and is due to end in March 2019 or until 200 patients are recruited, with a further 1 year period for follow up, data analysis and manuscript submission.

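### Table 1 ties one DASH limit of 30 to two reference periods, pre-operative for inclusion and pre-injury for exclusion, and the two must be reconciled

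*Protocol article*

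**What the plan says.** The eligibility rules are in Table 1, under Consent procedures. Inclusion criterion 2 reads "Pre-operative DASH score of 30 or less". Exclusion criterion 7 reads "Patients with impaired upper limb function prior to injury enough to have a DASH score of more than 30 points". The cut-off is the same and the time words differ.

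The scale is described under Secondary outcomes: "The DASH score has a range from 0 to 100 with higher scores representing greater disability". The same paragraph adds: "Subjects rate task difficulty regardless of hand dominance or affected side, thus reflecting their total upper-extremity disability".

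Two other sections fix when eligibility is judged. Study design defines the population as adults "presenting to the RAH with a closed distal radius fracture and who are considered for surgical treatment using volar plating". Recruitment approaches patients only once surgery by volar plating has been decided. Screening therefore always follows the fracture. Inclusion criterion 3 further requires shortening, dorsal tilt and an articular step beyond stated limits, so the fracture is a displaced one.

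Nothing in the article says that the DASH in inclusion 2 is a recalled score for the time before the injury.

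**The concern.** In a fracture trial, before surgery and before injury are different times. A DASH completed before surgery about current function is completed with a broken wrist, so it largely measures the fracture. A DASH about function before the injury measures prior impairment. Setting the same limit on both gives two tests that can disagree about the same patient.

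Two things are at stake. The first is consistent screening. The article names two roles at consent, a trained research associate (Consent procedures) and the orthopaedic trainee (Randomisation). If they read the entry differently, the enrolled population is not reproducibly defined. The second is recruitment: on the literal reading, the entry could exclude patients whom exclusion 7 was evidently written to keep.

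**Working it through.** **1. The two criteria side by side.**

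| Patient | Exclusion 7 (before injury) | Inclusion 2, read as current function before surgery | Inclusion 2, read as recalled pre-injury function |
|---|---|---|---|
| 30 or less before injury, 30 or less now | passes | passes | passes |
| 30 or less before injury, above 30 now | passes | **fails** | passes |
| Above 30 before injury | excluded | either result; excluded anyway | fails |

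The two readings of inclusion 2 change the eligibility decision only in the second row. That row holds patients with good prior function who are disabled by the fracture.

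**2. The plan's own sample size, reproduced.** Inputs from Sample size: difference 11.5, SD 20, alpha 5%, power 90%. Two-sided testing is from the Statistical analysis plan section.

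- Normal approximation: n = 2 × (1.960 + 1.282)² × 20² / 11.5² = 63.6, so 64 per group. The t-test version gives 64.5, so 65, as stated.
- Inflation: 65 × 1.5 = 97.5, so 98 per group, as stated. 2 × 98 = 196, against a recruitment target of 200.

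None of this depends on how the DASH limit is read.

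**3. The share of patients that must qualify.** From Setting: "The orthopaedic department manages approximately 200 cases of distal radius fractures with surgery annually". From Trial organisation: "The allocated recruitment period for the trial is 24 months".

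- Pool: 200 × 2 = 400 surgical cases.
- Share that must be eligible and consent: 200 / 400 = 50% (196 / 400 = 49%).

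The 400 counts all surgically managed cases, before the other criteria in Table 1 and before refusals, so it is generous to the plan. On the literal reading of inclusion 2, at most 400 × P(DASH ≤ 30) patients remain. That is below 200 whenever the median post-fracture DASH exceeds 30.

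**4. Illustration under assumed distributions.** The article gives no post-fracture DASH distribution. The means and SDs below are assumptions, and the normal form is only approximate on a scale bounded at 0 and 100. Formula: P(DASH ≤ 30) = Φ((30 − mean) / SD), multiplied by 400.

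| Assumed mean | SD 15 | SD 20 | SD 25 | Share excluded, SD 15–25 |
|---|---|---|---|---|
| 30 | 200 | 200 | 200 | 50% |
| 40 | 101 | 123 | 138 | 75% to 66% |
| 50 | 36 | 63 | 85 | 91% to 79% |
| 60 | 9 | 27 | 46 | 98% to 89% |
| 70 | 2 | 9 | 22 | 99.6% to 95% |

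The cells are patients left out of about 400. Example: mean 50, SD 20 gives Φ(−1.0) = 0.159, and 0.159 × 400 ≈ 63.

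**The case against.** The strongest defence is that the two labels are compatible. Pre-operative can describe when the score is collected, not which period the patient rates. Since enrolment always follows the fracture, even a pre-injury DASH has to be collected before surgery, by recall. The limits are exact complements, and exclusion 7 supplies the reference period. If inclusion 2 measured post-fracture disability, exclusion 7 would be almost redundant, because few patients above 30 before the injury would score 30 or less with a fracture. Recall instructions may also sit in the patient booklet or the case report form, which are not shown.

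Most of this stands as an account of intent: the mirror-image reading is plausible and probably what was meant. It does not remove the problem. Inclusion 2 does not state that reading, and two differently worded criteria invite the view that two quantities are meant. This is a conflict between two stated rules, not a detail left to a fuller document.

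Three stronger conclusions might be drawn, and the article supports none of them:

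- A reader might infer that the rule screens out most of the target population. That needs both the literal reading and a post-fracture median above 30, and the article gives no distribution.
- A reader might infer that an unclear entry score spoils a baseline covariate. The Statistical analysis plan section names no DASH covariate. The article uses DASH at entry only as an eligibility screen.
- A reader might infer bias between the plates. Eligibility is settled before randomisation, so either reading applies equally to both arms.

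**Conclusion.** The inconsistency is real and rests on the text of Table 1 alone: one limit, two reference periods, and a definable group of patients who pass one entry and fail the other.

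The recruitment consequence is conditional. It requires that inclusion 2 be applied to current function and that the median post-fracture DASH exceed 30. Under those conditions the target of about 200 from about 400 cases cannot be met, even with full consent. Over assumed means of 40 to 70 and SDs of 15 to 25, about 138 down to 2 patients would remain. Those counts illustrate the risk and are not estimates for this hospital.

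Severity is moderate. The wording decides who enters the trial and can make screening inconsistent, but it leaves the sample size calculation intact and does not bias the between-arm comparison.

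**What to change.** Reconcile the two entries in Table 1 by stating one reference period for the DASH limit. The direct way is to reword inclusion 2 as the complement of exclusion 7: a DASH of 30 or less for function before the injury, recalled by the patient and recorded at enrolment. The case report form and patient booklet should carry the same reference period, so that whoever screens the patient asks the same question.

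The cost is a one-line amendment and a check of the form. The downside is some recall error, but exclusion 7 already implies it, because pre-injury function can only be reported after the event. The sample size and the analysis do not change.

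If patients have already been screened when the amendment is made, record which reference period was used for them, so that the enrolled population can be described accurately.

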### Recruitment

All patients eligible for the study, and for whom a decision to undergo surgical treatment by volar plating has been made will be invited to participate. Following patient recruitment to the trial, patients will be randomised to receive one or other of the plates. Patients declining randomisation will be managed using the routine plating option, but will still be monitored longitudinally in the standard fashion, forming an observational arm of the study. Inclusion of the patient in the trial will be flagged on their clinical notes by means of a trial sticker. (See Fig. 1). Documentation of complications such as implant failure, revision to another plate system and cross over will be done.

